### Complementary investigations

#### In vivo tests

Skin prick tests to peanut will be performed before each DBPCOFC, including a positive (histamine hydrochlorhydre 10 mg/mL) and a negative (saline solution) control.

#### In vitro tests

The immunological profile will be monitored during the protocol before each DBPCOFC. Assays include total IgE and IgG 4 levels, peanut specific IgE and IgG4 levels for peanut and the following recombinant fractions: rAra h1, rAra h 2, rAra h3, rAra h8, rAra h9 (ImmunoCAP®, Phadia 250®, Thermofischer®). In addition, peanut specific basophil activation and degranulation will be assessed by a basophil activation test (CCR3, CD63, and CD203c, Flow CAST® and CD203c Reagent set, Bühlmann).

In addition, specific peanut IgE and IgG4 assays will be measured midway through the build-up phase. Cross-reactions will be evaluated during the initial assessment. Assays include specific IgE levels for lupine, walnut, almond, hazelnut, pistachio, sunflower, and Cross Carbohydrate Determinants (CCD). All samples will be stored at -80°C in a serum bank approved by the Agence Nationale de Securité du Médicament (ANSM) (2012-A01040-43).

### Judgment criterion

During each DBPCFC, peanut intake will be incremented every 30 min as follows: 10 mg, 20 mg, 40 mg, 80 mg, 160 mg, 300 mg, 500 mg, 890 mg, 2 g, 5 g. DBPCOFC will be considered positive at the threshold of 2 g if a patient exhibits at least one clinical objective sign of allergic reaction (dermatological, respiratory, gastrointestinal, or systemic involvement) within 30 min following the intake. If the patient reports subjective signs, 30 min can be added. Thereafter, the cumulative intake dose will be considered as the positive threshold of the OFC.

### Study endpoints

The main endpoint is the percentage of patients who satisfy to the judgement criterion, that is, negative DBPCOFC at the threshold of 2 g of cumulative intake of peanut at the end of the build-up phase of 24 weeks.

Secondary endpoints include:the percentage of patients with a negative DBPCOFC at the threshold of 2 cumulated g performed 6 weeks and 6 months after the end of the maintenance phase;the percentage of patients who quadruplet their reaction threshold between the first and the second DBPCOFC;the percentage of adolescents who have adverse effects during the build-up phase (degree and number of adverse events, use of rescue medication, rescue consultations; and hospitalizations);immunological profile confirming peanut desensitization (skin prick tests, peanut specific IgE and IgG 4, basophil activation test).

### Blinding

Indistinguishable peanut and placebo doses will be sent by the hospital pharmacy department. Investigators will not be aware of the treatment allocation of the patient, including during the DBPCOFC. A computer program will generate the coding list and will allocate coding numbers to patients from the specific trial site. In each participating center, the data will be collected and recorded onto case report forms (CRFs) by local research coordinators blinded to the randomized intervention. A trained research coordinator, also blinded to the randomized intervention, will centralize data from all sites and will record them onto an electronic database.

### Suspension of protocol

The protocol may be suspended for an individual patient if a severe adverse event occurs at any time during the protocol or if the patient cannot complete the build-up phase because of severe or repeated allergic reactions leading to prolonged stagnation at a given step.

The data monitoring safety committee will recommend interruption of the trial if a patient’s safety is compromised.

### Statistics

For this study, 60 randomized patients are necessary to detect a 50% difference in the primary outcome, at a two-sided α level of 0.05 and a statistical power of 90%, assuming a 60% rate of desensitization after the build-up phase in the treated group and 10% in the placebo group [8,9,14]. Assuming a successful completion of desensitization of 65%, 40 patients should be entered at the second randomization. n = 20 patients by group will provide a minimal statistical power of 80% to detect a relative difference of 30% after the maintenance phase.

Statistical analysis will be conducted on an intention-to-treat basis. Fisher’s exact test will be used for primary outcome analysis. Continuous variables will be compared with the unpaired t test or the Mann-Whitney test when appropriate. Owing to sample size, non-parametric tests will often be preferred. Longitudinal analysis using random-effects models will be performed to take into account between and within subject variability. All analyses will be conducted with Stata statistical software, version 13 (StataCorp LP, College Station, TX, US). A two-sided *P* value of less than 0.05 will be considered to indicate statistical significance.

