### Randomizations

After the initial DBPCOFC, attribution of active treatment (peanut) or placebo will be done by a first randomization (R1) at a ratio treatment/placebo of 2:1. Stratification will be performed every six participants. For the second randomization (R2), the ratio between the two groups will be set at 1:1. Randomizations will be stratified by location due to the multisite nature of the study.

Each patient will be identified by an identification number consisting of the number of permanent investigation center and an individual patient number. The patient number will be assigned chronologically on the randomization list. A comprehensive document describing the randomization procedure will be kept as confidential at the Children Clinical Research Centre, INSERM CIC 1405.

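### Sixty patients at 2:1 give about 98% power for the primary comparison, not the stated 90%: a minor, conservative misstatement whose basis should be given

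*Protocol article*

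**What the plan says.** The sample-size paragraph of the Statistics section states that "60 randomized patients are necessary to detect a 50% difference in the primary outcome". The level is two-sided 0.05, and the other conditions are: "statistical power of 90%, assuming a 60% rate of desensitization after the build-up phase in the treated group and 10% in the placebo group". The same section names Fisher's exact test for the primary outcome and an intention-to-treat analysis.

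The Randomizations section sets "a first randomization (R1) at a ratio treatment/placebo of 2:1", so 60 patients divide into 40 on peanut and 20 on placebo.

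The next sentence of the Statistics section makes a second demand on numbers: 40 patients at the second randomization (R2), with 65% assumed to complete desensitization successfully. The article states no allowance for drop-out.

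**The concern.** The paragraph gives every input needed to recompute the primary sample size and presents 60 as what those inputs require. A difference of 50 percentage points between 60% and 10% is very large, and 60 looks like more patients than 90% power would need.

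The validity of the primary test is not at stake. What is at stake is whether the justification is accurate. As worded, the text suggests that 60 sits at 90% power with no margin. A reader or the safety committee then cannot tell what the number is for, or how much loss the primary comparison can bear.

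**Working it through.** **Inputs.** Response 60% (active) and 10% (placebo), two-sided α = 0.05, power 90%, total 60, Fisher's exact test: all from the Statistics section. Allocation 2:1: from the Randomizations section. At 2:1, 60 patients are 40 + 20.

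**Step 1. Try to reproduce 60 with the usual formula.** With r = 2 active patients per placebo patient:

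- p̄ = (0.10 + 2 × 0.60)/3 = 0.4333, and p̄(1 − p̄) = 0.2456.
- n(placebo) = [1.960 √(1.5 × 0.2456) + 1.282 √(0.24/2 + 0.09)]² / 0.50² = (1.190 + 0.587)² / 0.25 = 12.6, rounded up to 13.
- Total 13 + 26 = **39**.

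With the continuity correction:

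- n′ = (12.63/4) × [1 + √(1 + 2 × 3/(12.63 × 2 × 0.50))]² = 15.5, rounded up to 16.
- Total 16 + 32 = **48**.

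Other settings do not give 60 either. Two-sided 1:1 totals for 90% power are 34 (uncorrected), 40 (exact Fisher) and 42 (continuity-corrected). One-sided totals are smaller. Even 95% power at 2:1 with continuity correction needs only 54.

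**Step 2. Power under the planned test.** Exact power is the sum, over all pairs of responder counts (a, b), of Bin(a; n active, 0.60) × Bin(b; n placebo, 0.10) where Fisher's two-sided p is below 0.05:

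| Active : placebo | Total | Fisher power |
|---|---|---|
| 26 : 13 | 39 | 89.0% |
| 28 : 14 | 42 | 92.0% |
| 30 : 15 | 45 | 91.4% |
| 32 : 16 | 48 | 93.1% |
| 40 : 20 | 60 | 97.8% |

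The small dip from 42 to 45 comes from the discreteness of the exact test.

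**Step 3. Normal-approximation check at 40:20.** The standard error under the null is √(0.2456 × (1/20 + 1/40)) = 0.1357. Under the alternative it is √(0.09/20 + 0.24/40) = 0.1025.

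- Uncorrected: (0.50 − 1.960 × 0.1357)/0.1025 = 2.28, power 98.9%.
- Continuity-corrected, with 0.50 reduced by (1/20 + 1/40)/2 = 0.0375: (0.4625 − 0.2660)/0.1025 = 1.92, power 97.2%.

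All three methods put 60 patients at about 98%.

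**Step 4. Size of the discrepancy.** Power: 97.8 − 90 = 7.8 percentage points. Number: 60 − 48 = 12 to 60 − 42 = 18 patients.

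**Step 5. What could lead to 60.**

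- Drop-out of 20% on the continuity-corrected figure: 48/(1 − 0.20) = 60. The 20% is an assumption and is not in the article.
- The R2 target: 40/0.65 = 61.5, or 60 × 0.65 = 39. This applies the 65% to all 60 patients, although only 40 are assigned to peanut.

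**Step 6. Power if losses count as failures.** The article specifies intention to treat but not how losses are scored, so this is an assumption. All 60 stay in the analysis and the response rates are diluted:

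| Loss | Rates if both arms are diluted | Fisher power | Rates if only the active arm is diluted | Fisher power |
|---|---|---|---|---|
| 20% | 48% v 8% | 91.0% | 48% v 10% | 85.9% |
| 25% | 45% v 7.5% | 87.9% | 45% v 10% | 79.9% |

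**The case against.** The best defence is that 60 meets the stated requirement and exceeds it. No error rate or decision rule is affected, and a condensed article may leave out a drop-out allowance given in the full protocol. Losses are foreseeable, since the article provides for exclusion or suspension after severe or repeated reactions, and 20% on 48 gives exactly 60. The R2 target also points to about 60. All of this stands, and it keeps the point minor. It does not rescue the sentence, which ties 60 to the effect size, α and power alone; on those terms fewer patients suffice.

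A reader might infer more than the document supports:

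- *That 60 is simply a wrong number, or that enrolment could be cut to 42–48.* The possible explanations above prevent the first conclusion. Cutting would remove the reserve against loss and leave fewer patients for R2.
- *That a 1:1 calculation was carried over, because 20 v 20 gives 90.8%.* That is 40 patients, not 60, and the article shows no 1:1 calculation.
- *That 60 was really set to supply R2.* The text attributes 60 to the primary outcome.
- *That 90% power survives down to 45 patients.* This holds only if the 45 who remain keep undiluted rates of 60% and 10%. With 25% loss from 60 scored as failure, power is 87.9% or 79.9%.

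**Conclusion.** The point holds as a minor correction. On the stated rates, α, 2:1 ratio and Fisher's exact test, 60 patients give about 98% power, and 90% needs about 42 (exact Fisher) to 48 (continuity-corrected). The claim that 60 are necessary for 90% is not reproduced by its own inputs.

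The misstatement is conservative and leaves the primary comparison unharmed. The 98% assumes that all 60 patients contribute at the full 60% and 10% rates. If 20% are lost and scored as failures, power comes back to between 85.9% and 91.0%, so part of the apparent surplus may be a sensible reserve that the text does not describe. Why 60 was chosen cannot be settled from the article.

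**What to change.** Restate the power along these lines: *60 patients (40:20) give about 98% power with Fisher's exact test for 60% v 10%, two-sided 0.05.*

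Then give the actual basis for 60: a drop-out allowance with its rate, the R2 target, or both. The sponsor has to supply this, because the article does not. If the R2 target is cited, say to how many of the 60 patients the 65% applies.

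If losses are to count as failures under intention to treat, quote power on that basis as well: with 20% loss at 40:20, 91.0% if both arms are diluted and 85.9% if only the active arm is. Do not add a claim that 90% power is kept down to 45 patients.

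The cost is a rewording of one sentence and a short statement of rationale. Enrolment, allocation and the primary test stay unchanged.

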## Methods/Design

### Objectives and design

The main objective is to investigate in an adolescent population the efficacy and safety of peanut oral escalating immunotherapy up to a maximum level of 2 g of peanut. The secondary objectives are to compare two maintenance durations (13 and 37 weeks) with 2 g daily of peanut intake, to investigate the immunologic effects of peanut oral immunotherapy, and to assess the safety of the procedure.

The study was designed in two phases: build-up and maintenance immunotherapy (Figure 1). After a baseline double-blind placebo-controlled oral food challenge (DBPCOFC), participants will be randomized (R1) in the build-up phase (24 weeks) to one of the two groups (treatment or placebo). At the end of the build-up phase, desensitized participants will be randomized (R2) for the maintenance phase (13 versus 37 weeks’ duration). During this second phase there will be no blinding.

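### The 40 patients expected at the second randomisation is 65% of all 60 randomised; the 2:1 allocation and the plan's own rates give about 26 to 28 (13 to 14 per group)

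*Protocol article*

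**What the plan says.** The figures stand in three sections of the protocol article.

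- **Statistics, primary outcome.** The plan states that "60 randomized patients are necessary to detect a 50% difference in the primary outcome", "assuming a 60% rate of desensitization after the build-up phase in the treated group and 10% in the placebo group".
- **Statistics, second randomisation (R2).** The next sentence reads: "Assuming a successful completion of desensitization of 65%, 40 patients should be entered at the second randomization". The paragraph then gives 20 patients per group at least 80% power for a relative difference of 30% after maintenance. It states no base rate.
- **Randomizations.** Peanut or placebo is assigned by a "first randomization (R1) at a ratio treatment/placebo of 2:1"; the caption of Figure 1 repeats this ratio. "For the second randomization (R2), the ratio between the two groups will be set at 1:1".
- **Objectives and design.** Entry to R2 depends on the result of the build-up: "desensitized participants will be randomized (R2) for the maintenance phase". Comparing 13 with 37 weeks of maintenance is the first secondary objective listed.

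**The concern.** The step from 60 randomised to 40 re-randomised appears to apply a success rate typical of the peanut arm to the whole trial. A third of the patients receive placebo, and the preceding sentence expects only 10% of them to be desensitised.

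The comparison of maintenance durations has its own randomisation and its own power statement, and the Background names maintenance length as something the trial sets out to investigate. If about a third of the planned R2 patients will not exist, the power claim for that comparison has no basis. A non-significant result with about 13 per group could then be misread as evidence that 13 weeks does as well as 37.

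**Working it through.** **Inputs.** 60 randomised; 60% (peanut) and 10% (placebo) desensitised; 65% successful completion; 40 at R2 and 20 per group (all from Statistics). R1 at 2:1 and R2 at 1:1 (Randomizations). R2 open to desensitised participants (Objectives and design).

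**Step 1: reproduce the stated figure.** 60 × 0.65 = 39, rounded up to 40. This works only when the base is both arms together.

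**Step 2: split by arm.** At 2:1, peanut = 60 × 2/3 = 40 and placebo = 60 × 1/3 = 20.

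**Step 3: expected entrants = sum over arms of (patients × rate).**

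| Assumption | Calculation | R2 entrants | Per group |
|---|---|---|---|
| 60% peanut, 10% placebo | 40 × 0.60 + 20 × 0.10 = 24 + 2 | 26 | 13 |
| 65% peanut, 10% placebo | 40 × 0.65 + 20 × 0.10 = 26 + 2 | 28 | 14 |
| 65%, peanut arm only | 40 × 0.65 | 26 | 13 |
| 60%, peanut arm only | 40 × 0.60 | 24 | 12 |

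No row comes near 40. Reaching 40 from the peanut arm alone would need every one of its 40 patients to succeed.

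**Step 4: allow for chance.** Take the number entering as the sum of two independent binomials, Bin(40, p) for peanut and Bin(20, 0.10) for placebo.

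- p = 0.60: mean 26, 5th to 95th percentile 20 to 32, P(at least 40) = 0.00002.
- p = 0.65: mean 28, 5th to 95th percentile 23 to 33, P(at least 40) = 0.00016.

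**Step 5: the number randomised that would supply 40.** At 60% and 10%, the entry fraction is 26/60, so 40 ÷ (26/60) = 92.3, or about 93 patients at 2:1. At 65% with the peanut arm alone, 40 ÷ 0.65 = 61.5 peanut patients, and 61.5 × 1.5 = 92.3 in total.

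**Step 6: what the lower number does to power.** The plan gives no base rate, so the rates below are assumptions and the difference is read as 30 percentage points. Two-sided test at 0.05; normal approximation, with exact Fisher power in brackets.

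| Assumed rates | 20 per group | 13 per group |
|---|---|---|
| 100% vs 70% | 78% (76%) | 58% (35%) |
| 95% vs 65% | 67% (59%) | 48% (31%) |
| 65% vs 35% | 47% (34%) | 33% (26%) |

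Read as a relative difference, 30% gives a smaller gap for any base rate below 100%: for 90% vs 63%, Fisher power is 41% at 20 per group and 22% at 13.

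**Step 7: the primary comparison.** With 40 and 20 patients at 60% and 10%, power is 99% by the normal approximation and 98% by Fisher's test, above the 90% claimed.

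**The case against.** Several points can fairly be made for the plan.

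- **Placebo patients might be offered the build-up later.** If all 60 eventually received peanut, 65% of 60 would be the right sum. The document is a condensed article and Figure 1 is not shown, so it cannot be said that crossover is ruled out. But none is described: the design text and the figure caption take participants from a successful build-up directly to R2.
- **Forty may be a requirement, not a forecast.** The wording allows this. Sixty randomised patients would still not supply it at the stated rates.
- **The 60% and 65% may be different quantities.** A reader might infer that the paragraph gives two rates for one event. The text does not establish that. The 60% is the desensitisation rate after build-up, while the 65% is called successful completion, and the procedures allow a dose level to be held for extra periods. Completing the build-up and passing the 24-week challenge need not coincide. The difference deserves a sentence of explanation, but it moves the answer only from 26 to 28.
- **Placebo patients can qualify.** A reader might infer that only the peanut arm can feed R2. The plan itself assumes 10% desensitisation on placebo, and R2 entry is not limited by arm. They add about 2 patients and are counted above.
- **It is a secondary comparison.** This is true, and it limits the consequence. The validity of the primary analysis is not in question.

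**Conclusion.** The concern holds. The planned R2 size of 40 (20 per group) contradicts the allocation ratio and success rates stated in the same document. The consistent figure is about 26 (13 per group), or about 28 (14 per group) if 65% is used for the peanut arm. That is a shortfall of 12 to 14 patients, roughly a third, and it is far outside chance variation.

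This rests on exact 2:1 allocation of 60 patients, on the plan's own rates, on no crossover before R2 (none is described), and on independence between patients for the probabilities.

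Two stronger readings should be resisted. First, the size of the power loss cannot be stated as a fact about this trial, because the base rate is not given. In the illustrations even 20 per group falls short of 80%, so correcting the number may not be all that the power sentence needs. Second, a reader might infer that R2 should be analysed in peanut-arm patients only. The documents do not support that as a correction: R2 randomises all desensitised participants and the analysis is by intention to treat, so it would be a change of analysis population.

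**What to change.** Limit the change to the sample-size paragraph under Statistics:

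1. Replace 40 patients and 20 per group with about 26 to 28 patients and 13 to 14 per group, showing the sum by arm.
2. Use one success rate for the peanut arm, or say what distinguishes the 60% from the 65%.
3. Restate the power, or the detectable difference, for 13 versus 37 weeks at that size. Give the assumed base rate and say whether the 30% is relative or absolute.
4. If placebo patients are in fact offered peanut before R2, describe that step and base the R2 number on it.

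The cost is a rewritten paragraph and a less favourable stated figure for a secondary comparison. No extra patients are proposed. The sponsor should accept knowingly that the maintenance comparison will be small: keeping 40 at R2 would take about 93 randomised patients at these rates. Nothing changes for the primary comparison.

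### For the 13- versus 37-week comparison, 80% power with 20 per group is at best a near-ceiling case, not a minimum

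*Protocol article*

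**What the plan says.** Comparing the two maintenance durations heads the list of secondary objectives (Objectives and design): "The secondary objectives are to compare two maintenance durations (13 and 37 weeks) with 2 g daily of peanut intake". Desensitized participants are randomized a second time for this purpose, and "the ratio between the two groups will be set at 1:1" (Randomizations).

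The Statistics section sizes the comparison in one sentence: "20 patients by group will provide a minimal statistical power of 80% to detect a relative difference of 30% after the maintenance phase". It does not say what success rate the 30% is taken from, which endpoint is meant or which test is assumed. The general rule is that "A two-sided *P* value of less than 0.05 will be considered to indicate statistical significance". Fisher's exact test is named, but only for the primary outcome.

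The only endpoint that Study endpoints expressly places after maintenance is binary: "the percentage of patients with a negative DBPCOFC at the threshold of 2 cumulated g performed 6 weeks and 6 months after the end of" that phase.

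**The concern.** A relative difference of 30% between two proportions does not fix the power. The power depends on the reference rate, and for a given relative difference it falls steeply as that rate drops below 100%. A sentence promising at least 80% therefore has to hold at every plausible reference rate, and with 20 per group that looked doubtful.

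The second randomization exists to make this comparison. If the true power is well under 80%, the trial could easily miss a real 30% loss of effect with one of the durations. Someone relying on the stated power would then give a null result more weight than it can bear.

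**Working it through.** **Inputs from the protocol article:** 20 patients per group and a 30% relative difference (Statistics); 1:1 allocation (Randomizations); two-sided 5% level (Statistics).

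**Assumptions, because the article does not state them:** the endpoint is the proportion with a negative challenge (Study endpoints); the better arm has rate p and the other 0.7p; p is unknown and was scanned from 1% to 100%.

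**Step 1. Try to reproduce 80% in the most favourable case, 100% versus 70%.**

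- *Fisher, two-sided.* The better arm is always 20/20. Against 15/20 the p-value is 0.047; against 16/20 it is 0.106. Power is therefore P(X ≤ 15), with X binomial (20, 0.70), which is 0.762.
- *Uncorrected chi-square, exact power.* 20/20 against 16/20 now counts (p = 0.035) and 17/20 does not (p = 0.072). Power is P(X ≤ 16) = 0.893.
- *Unpooled normal formula.* The standard error is √[(1.0×0 + 0.7×0.3)/20] = √0.0105 = 0.1025. Power is Φ(0.30/0.1025 − 1.96) = Φ(0.97) = 0.833. Required n for 80% is (1.96 + 0.8416)² × 0.21/0.09 = 18.3, so 19 per group.
- *Pooled normal formula.* With mean rate 0.85, power is Φ{[0.30√20 − 1.96√(2×0.85×0.15)]/√0.21} = 0.779. Required n is 22 per group.
- *Arcsine approximation.* Power is 0.956.

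So 80% is reproducible at this extreme by some methods, but not by Fisher or the pooled formula.

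**Step 2. Move the reference rate down.** Fisher and chi-square powers enumerate all 21 × 21 outcomes, weighted by the two binomial probabilities.

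| Better arm vs other | Fisher | Chi-square, uncorrected | Unpooled normal | Pooled normal | Arcsine |
|---|---|---|---|---|---|
| 100% vs 70% | 76.2% | 89.3% | 83.3% | 77.9% | 95.6% |
| 98% vs 68.6% | 66.5% | 80.0% | 77.4% | 71.9% | 81.7% |
| 95% vs 66.5% | 54.7% | 68.3% | 68.9% | 63.7% | 69.8% |
| 90% vs 63% | 41.2% | 54.5% | 56.5% | 52.3% | 55.6% |
| 80% vs 56% | 27.1% | 38.4% | 39.1% | 36.5% | 38.0% |
| 60% vs 42% | 11.7% | 18.6% | 21.1% | 20.2% | 20.8% |

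Over the whole scan the Fisher maximum is 76.2%, at p = 100%.

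**Step 3. Other readings of the 30%.** As 30 absolute points, the Fisher maximum is again 76.2%, with 58.9% at 95% versus 65% and 49.2% at 90% versus 60%. As a relative increase (p to 1.3p), the Fisher maximum is 50.5%, at 76.9% versus 100%.

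**Step 4. What 20 per group can detect.** From a 90% reference, Fisher power is 80.3% against 47% and 78.4% against 48%. An 80% chance of detection therefore needs a fall to about 47%. By the pooled formula, 80% power for a 30% relative difference needs 22 per group at 100% versus 70%, 38 at 90% versus 63% and 59 at 80% versus 56%.

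**The case against.** Four points on the other side deserve weight.

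- *The figure can be obtained.* A reader might infer from the Fisher result that 80% is unattainable by any sound method. That goes too far. At 100% versus 70%, the unpooled normal formula needs only 19 per group, and the uncorrected chi-square and arcsine calculations also exceed 80%. The sentence may describe a ceiling-case calculation badly. This stands, but it makes 80% a best case: every two-sided method in the table is below 70% by 95% versus 66.5%. A one-sided normal calculation gives 86.8% at the ceiling, but the article specifies two-sided testing.
- *Fisher's test is not assigned to this comparison.* That is correct, and it is the conservative choice. It is a natural assumption with groups of 20, since the article names no other test for proportions. The conclusion about the word *minimal* does not depend on it.
- *The endpoint is inferred.* The power sentence does not name one, and immunological measures are also taken before each challenge. For a continuous outcome, 20 per group give 80% power for a difference of about 0.886 standard deviations. A 30% difference in means would meet that if the standard deviation were at most about 0.30/0.886 = 34% of the reference mean. The article gives no such outcome or standard deviation, so the binary reading remains the natural one.
- *No equivalence claim is made.* A reader might infer that the sponsor intends to treat a non-significant result as showing that 13 weeks is as good as 37. Nothing in the article says so. The risk lies in how a stated 80% power may be used later.

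**Conclusion.** The claim of at least 80% power is wrong as written. On the binary endpoint with a two-sided 5% level, 20 per group never reach 80% by Fisher's test (maximum 76%). By less conservative methods they reach it only when the better arm succeeds in about 98–100% of patients. At 90% versus 63%, power is 41% by Fisher and about 54–57% by the uncorrected chi-square, arcsine and unpooled normal methods.

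The 76% bound does not depend on any assumed reference rate, but it does depend on Fisher's test. The 90% rate is my illustration, not the plan's. The conclusion takes 20 per group as given; how many patients actually reach the second randomization is a separate question. Because the comparison is a secondary objective and the primary sizing is untouched, this should be fixed but is not critical to the trial's main result.

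**What to change.** In the Statistics section:

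1. Delete the claim of a minimal 80% power.
2. State the sponsor's assumed success rate in each maintenance arm, the test for this comparison, and the resulting power with 20 per group. As a model of form only: by Fisher's test, power is 41% for 90% versus 63%, and 80% power from a 90% reference requires a fall to about 47%. The rates must be the sponsor's own.
3. Report the 13- versus 37-week comparison as a risk difference with an exact 95% confidence interval.
4. State that a non-significant result will not be read as equivalence of the two durations.

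The cost is rewording, with no change to treatment, visits or data collection. The downside is that the stated power becomes less favourable and the comparison is openly less conclusive.
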